**Fig. 1 Fig1:**
[figure not shown]
Trial workflow. Patients will be identified for recruitment by screening all patients receiving care in the ICU on a daily basis. Before enrolment, the fluid status is analyzed in cooperation with the attending physicians and optimized if necessary. After optimization is ensured, informed consent is obtained and the patient will be registered by randomization. Before initiating RRT, laboratory tests will be performed and different variables will be documented. In the ‘early’ group, RRT will be initiated immediately after randomization, whereas initiation of RRT in the ‘late’ group will be started only after reaching stage 3 of the KDIGO classification and/or if absolute indications for RRT are present. Patients randomized to ‘late’ but never reaching stage 3 will remain in the ‘late’ group for purposes of analysis. Laboratory tests will be analyzed and variables relevant for the assessment of illness severity will be recorded on day 1 to day 21, day 28, day 60, day 90 and 1 year

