### Power and sample size

Power calculations are performed based on the primary endpoint, i.e. the overall survival in a 90-day follow-up period. The primary efficacy analysis is intended to test whether early versus late initiation of RRT in intensive care patients with AKI results in different overall survival in a 90-day follow-up period.

An adaptive design based on a group sequential plan according to O’Brien and Fleming with one interim analysis and a global (two-sided) significance level α = 0.05 is applied (see below). The expected 90-day mortality rate in the control group with late initiation of RRT is 55 % (based on literature research [7–10, 20–24]). Differences between treatment groups are to be detected with a power of 80 %, if the 90-day mortality rate in the experimental intervention group with early initiation of RRT is 37 % or smaller. The expected treatment effect of 18 % is calculated on the mortality differences between the early and late groups resulting from the studies of our literature research [7–10, 20–24] (see Additional file 3). The interim analysis is conducted at the time when half of the total number of deaths has been observed (information rate 0.5). Follow-up of each patient will be 90 days. Resulting from these considerations, the interim analysis is performed after 53 deaths have been observed across both treatment groups. The final analysis is planned to be performed after 106 deaths have been observed in total across both treatment groups, i.e. assuming an average of 46 % mortality rate in the 90-day follow-up period, a total number of 106/0.46 = 230 patients across both treatment groups is included in the final analysis. This corresponds to 256 recruited patients, if an expected number of 10 % of recruited patients is assumed to be lost to follow-up and in the worst case has completely non-evaluable data. Power calculations are to be performed based on a two-sided inverse normal log-rank test [25], using ADDPLAN software (ICON, Dublin, Ireland).

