### Interim analysis

A group sequential plan according to O’Brien and Fleming with one interim analysis is established. In order to maintain a global significance level alpha = 0.05, the interim and the final analysis are performed on local significance levels of 0.0052 and 0.0480, respectively. Based on the group sequential plan, an adaptive design is applied, that admits two possible design changes after the interim analysis: i) the number of deaths of the final analysis will be re-calculated applying the inverse normal method [26]; and ii) the schedule and the number of further interim analyses may be modified applying the conditional rejection error probability (CREP) principle [27, 28].

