**Fig. 3 Fig3:**
[figure not shown]
Statistical analysis with per-protocol principle. Patients with protocol violation will be excluded in the analysis to analyze the effect of both treatment arms. Protocol violation is defined as: subjects in the early group who did not receive RRT in the early phase of AKI (KDIGO stage 2); and subjects in the late group who did not receive RRT, although KDIGO stage 3 was achieved

In a first approach, the primary outcome is evaluated (overall survival in a 90-day follow-up period) using a two-sided inverse normal log-rank test [21]. The only difference to the primary analysis is that a per-protocol approach is pursued instead of an intention-to-treat analysis.In a second approach, data are reduced from the original primary outcome to the binary outcome ‘90-day mortality from all causes’. The binary outcome is created in order to provide comparability to other published study results. It is evaluated using a two-sided Chi-squared test.

Further statistical analyses of the primary outcome will be performed in order to address the fact that study patients have different risk profiles at the time of RRT initiation. The efficacy of the experimental and the control treatment may differ depending on the patient’s risk profile. For example ‘high risk’ patients may benefit from experimental treatment with early initiation of RRT substantially compared to control treatment, whereas in ‘low risk’ patients the ‘late’ approach may be superior. In order to address these questions, multivariable statistical analyses will be performed using Cox regression. Overall survival is modelled as a function of baseline risk (determined by pre-randomization baseline data such as the patient’s age, Acute Physiology and Chronic Health Evaluation (APACHE) score and SOFA score, as well as the baseline medical condition, i.e. severe sepsis/use of catecholamines/refractory fluid overload/development or progression of non-renal organ dysfunction), RRT treatment and the interaction of baseline risk and RRT treatment. In three different model approaches, RRT treatment is expressed in terms of: i) a time-dependent covariate that impacts survival starting with the time of RRT initiation; ii) the randomized treatment group; and iii) the time to initiation of RRT.

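### Cox model i compares RRT started with not yet started, not early with late initiation, and is confounded by progression; model ii should answer the risk-profile question

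*Protocol article*

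**What the plan says.** The point arises in the protocol article, section Primary outcome analyses, in the text on multivariable Cox regression.

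- The question: "The efficacy of the experimental and the control treatment may differ depending on the patient’s risk profile". The example given is that high-risk patients may gain from early initiation while low-risk patients may do better with the late approach.
- The adjustment: "Overall survival is modelled as a function of baseline risk (determined by pre-randomization baseline data", for example age, APACHE and SOFA scores and the qualifying condition. RRT treatment and its interaction with baseline risk complete the model.
- RRT enters in three alternative ways. Model i uses "i) a time-dependent covariate that impacts survival starting with the time of RRT initiation", model ii the randomised group, and model iii the time to initiation. The three are not ranked.

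Two other places determine what model i measures. Under Treatment arms, early RRT begins within 8 hours at KDIGO stage 2. For the late arm, the Fig. 1 legend says that "initiation of RRT in the ‘late’ group will be started only after reaching stage 3 of the KDIGO classification and/or if absolute indications" are present; late patients who never reach stage 3 stay in the late group for analysis.

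**The concern.** The question is about two initiation strategies, but model i does not separate them.

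1. **Pooling.** Once a late-arm patient starts RRT, that patient has the same covariate value as an early-arm patient. Apart from the first hours of the early arm, the not-yet-started state consists of late-arm time before a trigger and late-arm patients who never trigger. The null hypothesis tested is that the hazard after starting RRT equals the hazard before or without it.
2. **Confounding by progression.** In the late arm the term switches on because the patient has worsened, and stays off in patients who are stable or recovering. Pre-randomisation covariates cannot capture that later course.

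The article presents the three models as parallel answers. If model i shows harm or no effect while model ii shows benefit, nothing in the text says that the randomised comparison takes precedence.

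**Working it through.** **Step 1: the plan's own figures.** Inputs from Power and sample size: 90-day mortality 55% (late) and 37% (early), power 80%, "global (two-sided) significance level α = 0.05 is applied", one interim look at half the deaths.

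- Implied hazard ratio: θ = ln 0.63 / ln 0.45 = 0.579.
- Fixed design (Schoenfeld): 4 × (1.960 + 0.842)² / (ln 0.579)² ≈ 105 deaths.
- Two-stage O'Brien–Fleming: 105.7 deaths, 80.1% power at 106, and "local significance levels of 0.0052 and 0.0480, respectively".
- Patients: 106 / 0.46 = 230; 230 / 0.90 = 256.

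All of these reproduce, and none depends on model i.

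**Step 2: hand calculation for model i.** Let π be the share of patients who progress (the same in both arms by randomisation) and ψ the factor by which progression multiplies the death hazard beyond baseline covariates. Simplify by treating late starts as quick relative to 90 days and ignoring depletion of high-risk patients. The started state then holds the whole early arm (weight 1) and the late progressors (weight π). The not-started state holds the late non-progressors.

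- RRT without effect: HR ≈ [(1 − π) + 2πψ] / (1 + π)
- Planned benefit attached to the early arm: HR ≈ {θ[(1 − π) + πψ] + πψ} / (1 + π)

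| π | ψ | HR, no effect | HR, planned benefit (0.579 by arm) |
|---|---|---|---|
| 0.2 | 1 | 1.00 | 0.65 |
| 0.2 | 1.5 | 1.17 | 0.78 |
| 0.2 | 2 | 1.33 | 0.91 |
| 0.5 | 1 | 1.00 | 0.72 |
| 0.5 | 1.5 | 1.33 | 0.98 |
| 0.5 | 2 | 1.67 | 1.25 |
| 0.9 | 1 | 1.00 | 0.78 |
| 0.9 | 1.5 | 1.47 | 1.15 |
| 0.9 | 2 | 1.95 | 1.53 |

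Example: π = 0.5, ψ = 2, no effect: (0.5 + 2) / 1.5 = 1.67.

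The article does not give π for the enriched population or ψ. Its only progression figure is 20% from stage 2 to stage 3 before enrichment (Discussion).

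**Step 3: simulation without those simplifications.** 230 patients, 1:1; early start uniform over 0–8 h; late start at progression plus 0–12 h; median 1 or 3 days to stage 3 (assumed); π from 20% to 100%; two-sided 5% tests; 600 trials per setting; large-sample hazard ratios from 400,000 patients. The values mostly fall below the hand calculation, as expected when high-risk patients die first.

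| | Model i | By randomised arm |
|---|---|---|
| No effect, ψ = 1 | HR 1.00 | HR 0.99–1.01 and significant harm in about 2–4%, over all no-effect settings |
| No effect, ψ = 1.5 | HR 1.14–1.45; significant harm 4–20% | as above |
| No effect, ψ = 2 | HR 1.26–1.86; significant harm 11–51% | as above |
| Planned, ψ = 1 | HR 0.64–0.75; power 8–64% | HR 0.57–0.59 and power about 76–85%, over all planned settings |
| Planned, ψ = 1.5 | HR 0.73–0.75 at π = 20%; 0.91–1.06 at π = 50–100% | as above |
| Planned, ψ = 2 | HR 0.82–0.83 at π = 20%; 1.06–1.42 at π = 50–100% | as above |

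One case in full: π = 50%, median 1 day, ψ = 2. With no effect, model i gives HR 1.61 and significant harm in 51% of trials. Under the planned benefit it gives HR 1.14 and finds benefit in 0.7%, against HR 0.59 and 76% by arm. A front-loaded hazard gives HR 1.52 with harm in 39%, and HR 1.09, respectively.

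A second simulation with its own settings gave, for π = 50% and ψ = 2, a no-effect HR of 1.53 with harm in 40% of trials, and a planned-effect HR of 1.09 with benefit found in 3% against 85% by arm. Without confounding, its planned-effect HR was 0.61–0.75 against about 0.55 by arm.

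**Step 4: the interaction term.** With an assumed true modification of −0.6 in log HR per SD of baseline risk and 50–90% triggering, interaction power was 14–40% in model i and 79–85% in model ii. False-positive rates for the interaction stayed near nominal in both.

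**The case against.** The best defence is that the correct analysis stands in the same sentence. Model ii uses the randomised group, the confirmatory test is the intention-to-treat log-rank test, and the Cox models are described only as further analyses. The paragraph opens by referring to risk profiles when RRT is initiated, and the abstract announces treated analyses, so an exposure term beside the randomised one is a recognisable complement. If RRT lowered the hazard equally whenever it was started, model i would be close to correct for that effect. All of this stands, and it limits the consequence. It does not make model i an answer to the early-versus-late question, and the article does not tell the reader which model has priority.

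Three stronger readings are tempting, and the documents do not support them.

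- *Model i misses most of the planned benefit.* Not unconditionally. With ψ = 1 it keeps 52–83% of the log hazard ratio. At 20% progression the estimate still favours early initiation for ψ of 1.5 or 2.
- *Model i will report false harm.* Only if progression raises the hazard beyond the baseline covariates. With ψ = 1 the no-effect HR is about 1.
- *The risk-profile test gives spurious interactions.* Its false-positive rate stays near nominal; the loss is power.

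The text says when the term begins to act and does not say that it switches off. Started versus not yet started is therefore the accurate description, rather than RRT running versus not running.

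**Conclusion.** The concern holds in a limited form. That model i makes a different comparison, and that its late-arm starts are triggered by worsening, follows directly from the article. The size of the bias does not: it rests on assumed progression shares of 20–90% and hazard multipliers of 1.5–2. Within those, false harm appears in about 4–40% of trials, or up to 51% in the simulation tabulated above, against 2.5% nominal. The planned benefit is weakened, and is cancelled or reversed when about half or more of patients progress. With no residual confounding, attenuation and loss of power remain. The primary conclusion, the alpha levels and the 106 deaths are untouched. This is a point to correct in a supporting analysis, because a biased answer is listed on equal terms with a randomised one.

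**What to change.** State that model ii (randomised group, baseline risk and their interaction) is the model that answers whether early-versus-late efficacy depends on risk profile. Drop model i, or report it only as a non-randomised analysis of RRT exposure, confounded by progression, from which no early-versus-late conclusion is drawn. This costs one or two sentences and needs no new data or patients.

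If an analysis of treatment received is still wanted, a weighted comparison of the two strategies that adjusts for recorded post-randomisation severity is an option. It has wider intervals, needs extra programming and assumes no unmeasured confounding. The article describes the recorded data by group (laboratory tests and severity variables on days 1 to 21, SOFA daily while in the ICU) without naming every trigger variable, so availability should be confirmed first.

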### Enrolment

Enrolment began in August 2013. Prior to being randomized into the study, the trial coordinators obtain consent for participation in the study (see Ethics and consent). Assuming all inclusion criteria are fulfilled and no exclusion criteria are met, each patient receives a study identification number and treatment allocation at enrolment. Patients are randomized in a 1:1 ratio to one of the two treatment arms using a computerized system. Randomization is stratified by SOFA Cardiovascular organ Failure Score (0–2 vs. 3–4) and by the presence or absence of oliguria. The randomization day is day 0.

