### Treatment arms

Early initiation of RRT will be initiated at stage 2 of the KDIGO classification within 8 hours:Urine output <0.5 ml/kg/h for ≥12 h; and/orTwo-fold increase of the serum creatinine level compared to the baseline value.

Late initiation of RRT will be initiated when stage 3 of the KDIGO classification (not later than 12 hours after achieving stage 3) is achieved:Urine output <0.3 ml/kg/h for ≥24 h; and/or > Three-fold increase of the serum creatinine level compared to the baseline value; and/orSerum creatinine of ≥4 mg/dl with an acute increase of at least 0.5 mg/dl within 48 hours.

Or if any of the following absolute indications for RRT are present:Urea serum levels >100 mg/dl;Potassium serum levels >6 mmol/l and/or ECG abnormalities;Magnesium serum levels >4 mmol/l;Urine production <200 ml/12 h or anuria (without diuretics, according to the KDIGO recommendations); andOrgan edema in the presence of AKI resistant to diuretic treatment (one attempt with loop diuretics prior to randomization).

After enrolment, ELAIN investigators are responsible for the catheter insertion and the initiation of RRT (see Additional file 1). Daily visits will be performed to ensure adherence to the protocol. Hemodynamic, pulmonary, inflammation, renal and laboratory data will be documented. Education to ensure proper implementation of the study protocol was done prior to starting enrolment. Project manager and trial investigators conduct monthly conferences to monitor all aspects of the protocol.

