The study design contains a specific protocol that tends to minimize unnecessary RRT trying to prevent patients from avoidable RRT-related risks and improve patients’ outcome. In 2012, the KDIGO group published the KDIGO criteria for diagnosing AKI [6]. It has been shown that only 20 % of patients who develop KDIGO stage 2 progress to KDIGO stage 3 [30]. Sepsis and other severe conditions (e.g. hemodynamic instability manifested by hypotension requiring vasopressor support, refractory fluid overload) have been shown to be important risk factors for developing dialysis-dependent AKI [31, 32]. Therefore, the inclusion criteria chosen for the ELAIN trial were selected to identify patients who are at high risk for the need of RRT. In addition, we chose a biomarker-based model for the detection of patients with worsening AKI, because previous studies demonstrated that biomarkers can be used for identifying potential aggravation [16]. By using this patient-enrichment strategy, we excluded patients whom subsequently recovered from AKI spontaneously without requiring RRT. Plasma NGAL is one of the most studied biomarkers in the field of AKI. The diagnostic value for the detection of AKI might be controversial [33, 34] but for the need of RRT in critically ill patients it has been demonstrated as a good predictor [35, 36]. Thus, to reduce the risk of unnecessary RRT, we only include patients with KDIGO stage 2, concomitant disorders and elevated NGAL values [35].

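### Cox model iii enters time to RRT initiation as a covariate from randomisation, so its timing coefficient can be biased even when timing has no effect

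*Protocol article*

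**What the plan says.** In Primary outcome analyses, after the per-protocol analyses, the article plans multivariable Cox models of overall survival. The terms are baseline risk, "RRT treatment and the interaction of baseline risk and RRT treatment". RRT treatment is expressed in three ways:

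- model i: "a time-dependent covariate that impacts survival starting with the time of RRT initiation"
- models ii and iii: "ii) the randomized treatment group; and iii) the time to initiation of RRT"

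Only model i is described as time-dependent. For model iii the article gives no landmark, no change of time origin and no value for patients who never start.

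Four other places determine what the covariate in model iii means:

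- Enrolment sets the clock: "The randomization day is day 0".
- Treatment arms, early group: "Early initiation of RRT will be initiated at stage 2 of the KDIGO classification within 8 hours".
- Fig. 1, late group: RRT "will be started only after reaching stage 3 of the KDIGO classification and/or if absolute indications for RRT are present".
- Fig. 1 also foresees late patients who do not progress: those "never reaching stage 3 will remain in the" late group for analysis.

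The first paragraph of Primary outcome analyses gives confirmatory status to the intention-to-treat analysis of the primary outcome.

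**The concern.** Read as written, model iii regresses survival from day 0 on a quantity that is not known on day 0. Three problems follow.

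1. **Immortal time.** A patient recorded as starting on day 3 cannot have died before day 3, yet counts as at risk with that value from day 0.
2. **Confounding by indication.** In the late arm the start is triggered by worsening disease. How soon it comes carries prognostic information that has nothing to do with any effect of timing.
3. **Undefined values.** A late patient who recovers or dies before a trigger has no start time. Dropping these patients breaks the randomised comparison. Giving them a value taken from follow-up makes the covariate partly a copy of the outcome.

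At stake is the purpose of these models: to say whether high-risk patients gain from early RRT while low-risk patients do as well or better with the late strategy. A timing term with a built-in bias, and an interaction resting on it, could supply such a message without any real effect.

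**Working it through.** **The plan's own figures, reproduced first.** The article states no figure for model iii, so the check takes its size from the sample-size section.

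- Hazard ratio from 37% and 55% mortality: ln(1 - 0.37) / ln(1 - 0.55) = 0.579.
- Two-stage O'Brien-Fleming plan, two-sided 0.05, information 0.5: local levels 0.0052 and 0.0480, as stated.
- Deaths for 80% power: 4 × 2.812² / (ln 0.579)² = 105.7, so 106, as stated.
- Patients: average mortality (55 + 37)/2 = 46%; 106/0.46 = 230; 230/(1 - 0.10) = 256, as stated.

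**Structure.** Let W be time from randomisation to RRT start and T survival time. W is observed only if W < T. Among observed starters, nobody with W > u can die at time u, yet all are in the risk set at u. This bias alone pushes the hazard ratio per day of delay below 1. If never-starters have better prognosis and are dropped, the remaining late patients are sicker than the whole early arm, which pushes it above 1. The net direction depends on the mix.

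**Null simulation, short delay.** Assumptions not in the article: Weibull survival with shape 0.7; early start at 0.1-0.33 day; late start at 0.3 day plus an exponential time with mean 1 day (about 1.3 days on average); a share of patients who recover and would never be triggered, with death hazard 0.4 of the rest unless stated. Timing has no effect, so the true hazard ratio is 1. Each scenario has 230 patients, 46% mortality and 500 runs, with start time as the only covariate.

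Never-starters dropped:

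| Recover without trigger | HR per day | p < 0.05 |
|---|---|---|
| 0% | 0.963 | 5.6% |
| 5% | 0.980 | 4.0% |
| 10% | 0.985 | 2.8% |
| 20% | 1.012 | 4.4% |
| 30% | 1.045 | 7.8% |
| 30%, hazard 0.25 | 1.08 | 10.6% |

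With 500 runs, the simulation error around a true 5% is about ±1.96 × √(0.05 × 0.95/500) = ±1.9 points. Only the last two rows lie clearly above nominal, but the estimate drifts from one side of 1 to the other.

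Never-starters given their own follow-up time as start time: 21% rejection with 10% recovering, and 89-92% with 20% recovering (HR about 0.98 per day). With very few never-starters, rejection is near nominal (about 7%).

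Never-starters coded at day 90, with nobody recovering: HR 1.05 per day, because early deaths become the latest starters. The coding alone reverses the direction.

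**Second simulation, different assumptions.** Early start uniform over 0-8 h; late start exponential with median 1, 3 or 7 days; 60-100% of late patients eligible to start; Weibull shape 1.0 or 0.6; 1,000 runs.

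- Never-starters dropped: HR 0.94-0.99 per day; rejection 3-5% at a 1-day median, 4-15% at 3 days, 8-38% at 7 days.
- Follow-up time as start time: 3-51% rejection when 90-100% are eligible, 78-98% when 60% are.
- Comparators: randomised arm (the model ii idea) 4-6%; time-dependent RRT status (the model i idea) 2-6%.
- Sicker patients progress faster, severity unadjusted, 90% eligible, never-starters dropped: 37%, 49% and 70% at medians of 1, 3 and 7 days; the randomised comparison stays at about 5%.

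**The case against.** The strongest reply is that the large rejection rates come from choices the article never makes. It does not say that never-starters receive their follow-up time, and such coding is commonly left to the full protocol or analysis plan. With a late delay of about a day and never-starters dropped, false positives barely rise. High rates need follow-up-based coding, delays of several days, or a severity link left unadjusted. **This stands.** A reader might infer that model iii will show a false timing effect in about 90% of null trials; the document does not support that.

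It can also be said that the simulated model is not the planned one, which adjusts for age, APACHE, SOFA and baseline condition and includes an interaction. **This stands too.** Adjustment would remove part of the severity effect, though not the immortal time or the missing values. No interaction was computed, so the interaction can be called unprotected by randomisation but not shown to be biased by any amount.

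The never-start share is uncertain. The Discussion says that 20% "of patients who develop KDIGO stage 2 progress to KDIGO stage 3", and a reader might infer that most late patients would never start. That figure describes patients before enrichment by NGAL and concomitant conditions. It also concerns stage 3, whereas any absolute indication triggers late RRT as well. It does not give the never-start share in this trial.

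Finally, the models are supportive, and model ii with the risk interaction is already planned. That limits the consequence.

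What does not stand is that this is only an omitted detail. No coding rule makes a fixed start-time covariate from day 0 valid: dropping never-starters selects on the future, and assigning a value ties the covariate to outcome or prognosis.

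**Conclusion.** The concern holds in limited form. Model iii is wrong in form, and the article's own rules for the late arm show why.

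Its size is conditional. With a short late delay and start time as the only covariate, the null hazard ratio per day lies between about 0.96 and 1.09 with 3-11% rejection if never-starters are dropped. With a follow-up-based value, rejection runs from about 7% to over 90%. The result rests on the assumed never-start share, the prognosis of those patients, the late-arm delay and the coding, none of which the article fixes.

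Two further inferences are not supported. The bias does not always make later start look protective: its direction changes with the handling of never-starters. Nor is the trial's main conclusion at risk, because the confirmatory log-rank test, its local levels, the 106 deaths and the sample size do not depend on this model.

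Model i avoids immortal time, but RRT start in the late arm is confounded by indication, so it does not give a causal timing effect either. Model ii alone keeps the randomisation.

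**What to change.** - Remove model iii. If a timing analysis is wanted, replace it with a landmark analysis, or with a clone-censor-weight analysis that compares start strategies from randomisation. State in advance how never-starters are included.
- State that the conclusion on baseline risk by treatment is drawn from model ii.
- Report model i as exploratory, noting that RRT start in the late arm follows deterioration.

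Both replacements need assumptions of their own. A landmark analysis describes only patients alive at the landmark. Weighting relies on recorded severity explaining the start of RRT; Fig. 1 already plans to record severity variables on days 1 to 21.

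The cost is analysis-plan wording and either a little more analysis work or one supportive analysis fewer. No new data are needed, and the sample size and primary test do not change.
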